## Abstract

**Background:**

In vitro fertilisation (IVF) treatment provides an opportunity to study early developmental responses to periconceptional dietary interventions. Retrospective studies have suggested links between preconception diet and fertility, and more recently, a "Mediterranean" diet has been reported to increase pregnancy rates by up to 40%. In addition, a prospective study examining increased intake of omega-3 polyunsaturated fats demonstrated a quickened rate of embryo development after IVF. However, up to now, few prospective randomised controlled trials have investigated the impact of periconceptional dietary interventions on fertility outcomes.

**Methods and design:**

The study is a randomised controlled trial of a dietary intervention consisting of olive oil for cooking, an olive oil based spread, and a daily supplement drink enriched with Vitamin D (10 microgram daily) and marine omega-3 fatty acids (2 g daily) for 6 weeks preconception versus a control diet of sunflower seed oil for cooking, a sunflower oil based spread, and a daily supplement drink without added Vitamin D or marine omega-3 fatty acids. Couples undergoing IVF will be randomised to either the intervention or control group (55 in each arm). The primary endpoint is embryo developmental competency in vitro, measured by validated morphokinetic markers. Secondary outcomes will include the effect of the dietary intervention on the nutritional content of the intrauterine environment.

**Discussion:**

This approach will enable rigorous examination of the impact of the dietary intervention on early embryo development, together with the influence of the peri-implantation intra-uterine nutritional environment.

**Trial registration:**

ISRCTN50956936

## Background

Large prospective cohort studies have demonstrated the impact of female and male preconceptional nutritional status on fertility, perinatal and long term health of the offspring
[1]. More recently, research has shown that variations in preconceptional diet may impact IVF outcomes. A ‘Mediterranean’ diet high in vegetable oils, fish, vegetables and legumes and low in carbohydrate-rich snacks was positively associated with red blood cell folate and vitamin B6 in blood and follicular fluid and with a 40% increase in the probability of pregnancy
[2]. The findings of a subsequent case control study by another research group also suggested that fertility outcomes were improved in couples with a Mediterranean diet
[3]. In a further prospective study of the association between dietary intake of polyunsaturated fatty acids, significant correlations were observed between the reported dietary intake of the omega-3 fatty acids (FAs) alpha-linolenic acid and docosahexaenoic acid (DHA) and embryo morphology after IVF
[4]. Despite this, no large prospective randomised intervention studies have investigated the impact of optimising the periconceptional diet on fertility outcomes, perinatal or child health outcomes
[5]. Moreover, it remains unclear by which mechanisms nutritional modifications act to impact embryo quality, implantation and subsequent periconceptional and perinatal development.

One reason for the lack of data from intervention studies derives from the challenges involved in encouraging and monitoring compliance to specific dietary regimens, particularly when the intervention is rigorous and/or of long duration. However, recent data, primarily from rodent studies demonstrate that dietary manipulations within a very short window around the time of implantation can have profound effects on early development
[6]. Administration of a maternal low protein diet during the 4 days of mouse pre-implantation development, followed by a control diet thereafter resulted in clear adaptive responses such as altered blastocyst numbers, upregulation of endocytosis into the yolksac, and an increase in the rate of trophoblast invasion. While these adaptive responses were observed to protect growth, they appeared to come at the cost of hypertension and abnormal behaviour patterns in adulthood
[7]. Another group has shown that administering a high fat diet in this short period results in altered zygote viability
[8], while treating with an insulin sensitizer during this period normalises the effects of obesity on oocyte quality and developmental competence
[9].

While extrapolation from rodents to humans brings uncertainties, this work suggests that a relatively brief dietary intervention in the 6 weeks prior to conception could have measureable effects on biomarkers of gamete and embryo health, the intra-uterine nutritional environment, and subsequent fetal and placental development, with implications for the long-term health of the offspring. Such a short period is likely to increase willingness to take part in a dietary intervention study and improve compliance during the intervention period. In addition, some lipid pools will have achieved maximal, or near-maximal, changes in eicosapentaenoic acid (EPA) and docosahexaenoic acid (DHA) content within 6 weeks
[10].

Studying the impact of short-term interventions in the general population is complicated by the difficulty of accessing couples in this preconceptional phase, and the relatively low probability of subsequent conception within one or two months of completing the intervention. These challenges are markedly alleviated in a population attempting to conceive by means of assisted conception techniques. Couples reporting for fertility treatment are readily accessed in the periconceptional phase, and have on average a 30% chance of conceiving in their first cycle of treatment. It is therefore feasible to study the impact of a relatively short dietary intervention, which by virtue of its limited duration is more likely to be adhered to for the duration required.

A further advantage of this model is the unique access IVF treatment gives to human gametes, embryos and the peri-implantation uterine environment. IVF offers a window on how the complex biological processes in early human development are affected by nutritional status. At the time of oocyte retrieval in IVF, follicular fluid and blood can be sampled and analysed for nutritional biomarkers. Since the fate of the oocyte can be followed in terms of morphology, fertilisation and embryo development, direct correlations between the nutritional environment of the developing oocyte and spermatozoa and IVF outcomes can be ascertained, as our group and others have shown previously
[11]. At the oocyte level, high fat diets in rodents have been shown to lead to lipid accumulation and endoplasmic reticulum (ER) stress
[12], while follicular fluid folate levels have been shown to correlate to embryo quality
[13].

Embryo quality can be assessed in terms of implantation potential on the basis of morphological and developmental criteria. The recent availability of incubators fitted with time lapse video monitoring technologies represents a step change in the ability to time precisely when key milestones of development are reached (‘morphokinetics’). This non-invasive means of interrogating early human development is enhanced by the generation of a video of each embryo allowing detailed analysis of development markers at a later date
[14]. In addition, analysis of embryo conditioned medium provides further non-invasive means of assessing the impact of periconceptional diet on embryo metabolism
[15].

Recent techniques developed by our group also allow us to analyse the impact of preconceptional diet on the intra-uterine environment. We have previously demonstrated the utility and practicality of aspirating endometrial secretions at the time of embryo transfer, which allows the study of the immediate intrauterine environment encountered by the embryo
[16]. It is now clear that uterine secretions have a key role in providing nutritional support for the pre-implantation embryo and recently the role of female reproductive tract fluid composition on developmental origins of later health has been highlighted
[17]. Current work is investigating the amino acid and glucose content of human endometrial fluid. Moreover, we have developed in-vitro models of embryo-endometrial interaction which provide the means to study the impact of nutritional interventions on embryo-endometrial signalling using donated cryo-preserved embryos
[18–20].

These approaches will enable rigorous examination of the impact of the dietary intervention on early embryo development, and the peri-implantation intra-uterine nutritional environment. Should a significant positive impact of a dietary intervention on early development be demonstrated, this would have major implications for health policy and strengthen arguments for the provision of preconceptional nutritional advice to the general population. The data generated will inform new approaches to improving preconceptional nutrition, and provide the basis for a major prospective community based intervention study aimed at determining the effectiveness of relatively short, low cost and feasible dietary intervention on pregnancy outcomes and child health.

This study will be conducted in compliance with the protocol, GCP and the applicable regulatory requirements.

## Methods and design

### Study objective

Although retrospective studies have suggested a link between preconception diet and human fecundity, several questions still remain for example which nutrients are beneficial and how long they need to be taken prior to conception. This prospective, randomised, controlled trial (the PREPARE trial (PREconception dietary suPplements in Assisted REproduction)) aims to address the questions of the effect of a diet rich in marine omega-3 FAs and Vitamin D on a developing embryo and the intrauterine environment.

### Hypothesis

Our hypothesis is that a diet rich in marine omega-3 FAs and Vitamin D will be beneficial to a developing embryo and thus improve morphokinetic markers used to predict embryo viability and implantation. Further to this, it is thought that this diet will affect the nutritional content of the intrauterine environment and alter the endometrial tissue immune cell populations.

### Study population and recruitment

Women participating in the PREPARE trial will be between the ages of 18 and 41 years, with a body mass index (BMI) between 20 and 32 kg/m^2^, and undergoing their first or second cycle of IVF or in vitro fertilisation – intracytoplasmic sperm injection (IVF-ICSI). Their partners must be using their own sperm and be prepared to provide a fresh sample prior to the dietary intervention and on the day of oocyte retrieval (they should not be using frozen sperm or sperm obtained by surgical retrieval). Additional inclusion criteria include an anti-műllerian hormone (AMH) of greater than 7 pmol/l or an antral follicle count (AFC) of more than 10. Participants must be willing to provide written informed consent to participate in the study.

Exclusion criteria are: any medical contraindication to IVF or IVF-ICSI treatment or to a specific dietary intervention, previously diagnosed diabetes, taking prescribed medication or herbal remedies apart from simple painkillers, and eating oily fish (as defined by the UK Food Standards Agency) more than once a week.

Eligible patients will be informed about the PREPARE study during information evenings or their initial consultation with the medical team. A minimum reflection period of 3 days will be offered. Eligible patients who wish to participate will be randomised after providing written consent. If an eligible patient declines participation, basic characteristics will be obtained to identify any selection bias (Figure 
1).

**Figure 1 Fig1:**
[figure not shown]
**Flowchart of eligible patients.**

### Study design

The PREPARE trial is a single centre, randomised controlled trial, powered to demonstrate a difference in mean duration of the second cell cycle (CC2) of embryos generated by IVF after exposure of the couple to the intervention versus control. Both the male and female in the intervention group will receive a six week diet of olive oil for cooking, an olive oil based spread, and a daily supplement drink enriched with Vitamin D (10 micrograms) and the marine omega-3 FAs EPA (1 g) and DHA (1 g daily) versus the control diet of sunflower seed oil for cooking, a sunflower oil based spread, and a daily supplement drink without vitamin D, EPA or DHA.

Following inclusion into the study but prior to randomisation, consenting participants will be invited to complete a preconception questionnaire and the short Southampton Food Frequency Questionnaire (FFQ) in order to characterise their lifestyle and diet prior to entry into the study
[21]. At this time, samples of blood, uterine fluid and endometrium will be obtained from the women in order to provide baseline data of the nutritional and immune cell content prior to the intervention. The male participants will be asked to provide a semen sample which will be analysed for concentration, motility and morphology according to the WHO criteria
[22].

The women embarking on the study will undergo ovarian stimulation according to our standard protocol, provided no abnormality is seen on their baseline scan on day 2 of their cycle. Oocyte retrieval will be performed 36 hours following the single dose of human chorionic gonadotrophin (hCG), which promotes oocyte maturation. At the point of oocyte retrieval, further blood will be taken from the female participants and the follicular fluid and cumulus cells that are routinely removed, during IVF-ICSI, from the oocyte prior to insemination will be snap frozen. A further semen sample from the males will be analysed according to the WHO criteria prior to insemination.

The embryos will be cultured in Vitrolife IVF media in a validated time lapse incubator (Embryoscope, Unisense, FertiliTech, Denmark) in 5% CO2, 5%O2 and at 37°C. During the incubation, twenty one plane focal images will be generated every hour and analysed according to morphological and morphokinetic markers
[23]. For women in whom embryo transfer is possible, uterine fluid aspiration will be carried out prior to the procedure. In those not undergoing embryo transfers, an endometrial biopsy will also be performed.

Compliance with the diet will be monitored by a daily diary completed at home by the couple and by counting the empty cartons when they are returned to the Fertility Unit (Figure 
2).

**Figure 2 Fig2:**
[figure not shown]
**Flow chart of study design.**

A recent systematic review of current literature and trial registers identified no other randomised controlled trials (RCTs) addressing this subject.

### Primary and secondary endpoints

The primary endpoint is the mean period in hours for the cleaved embryos from participants in each arm of the study to develop from the 2 cell to the 3 cell stage (CC2). Secondary endpoints include using the Embryoscope to examine embryo quality, including S2 (synchrony during second set of cleavage divisions), T5 (time between fertilisation and the five cell embryo formation)
[14, 24], CC3 (duration of the third cell cycle)
[24], and the appearance and disappearance of the pronuclei
[25]. Nutritional markers, including the concentration of fatty acids, Vitamins D, B12, and B6, folate, prostaglandin E2 (PGE2) and prostaglandin F2α (PGF2α) will be measured in blood, endometrial fluid and follicular fluid pre and post intervention. Changes in endometrial tissue immune cell populations will also be examined. In male participants, changes in semen quality pre and post dietary intervention will be recorded according to standard parameters.

Implantation rates and pregnancy outcomes will be recorded and analysed. These include antenatal ultrasound markers; such as crown-rump length at 7 weeks and 12 weeks and fetal head and abdominal circumference, femur length and cross sectional metaphyseal area and placental volume at 20 weeks gestation. Perinatal measurements including birthweight and length and placenta dimensions and weight will also be recorded. Participants will be invited to bring their neonate to undergo a Dual energy X-ray Absorptiometry (DXA) to measure bone mineral content and density soon after birth.

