### Statistical analysis

#### Sample size and power considerations

In a previous retrospective study from our group, a diet rich in the omega-3 FAs was shown to be associated with improved embryo morphology when assessed on day 3 post fertilisation. Using a published scoring system between 1 (highest quality) and 5 (lowest quality), embryos generated in women with a daily mean total intake of omega-3 FAs in the 4 weeks prior to IVF greater than 1.7 g scored a mean of 0.6 (SE 0.26) points higher than those embryos derived from a woman reporting an intake of <1 g per day. Recently, morphokinetic analysis of human embryos has shown the duration of key development phases to be correlated to standard conventional morphological criteria, but more highly predictive of implantation potential
[14, 26]. One of the most sensitive predictors of implantation has been shown to be CC2. Embryos with a CC2 shorter than 11.9 hours (pooled SD 2.25 hours, but not normally distributed) have been reported to have an implantation rate of 35% compared to 28% when this key developmental step took longer than 11.9 hours. Moreover, in a study correlating morphokinetic parameters with static morphology scoring, a CC2 less than 11.9 hours was shown to correlate with an overall increase in embryo score of 0.5 points on a 5 point scale
[14]. This is similar in magnitude to the impact on embryo morphology reported to be achieved by exposure to a high omega 3 FA diet as described above
[4].

The primary end point of this study is therefore the difference in mean CC2 score of embryos generated by IVF after exposure of the couple to the intervention versus control diet. In order to detect a minimum absolute difference of 12% (1.4 hours) in mean CC2, or effect size of 0.670, with power ≥80% at p <0.05 a non-parametric comparison (Wilcoxon test) indicates a requirement of 46 couples per group in the analysis.

To allow for drop outs and failure to produce sufficient viable embryos, a further 20% will be recruited. This requires the randomisation of a minimum of 55 couples per group (110 in total).

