### Data analysis

In order to adjust for pre-defined confounders such as age, AMH level, ovarian stimulation method, fertilisation method and the number of oocytes obtained, univariate and multivariate analyses will be performed. This will enable the independent contribution of the dietary factor to the primary and secondary outcome measures to be quantified.

Differences in embryo quality parameters will be tested by Wilcoxon testing, and differences in blood and endometrial fluid levels of the stated secondary outcome parameters will be tested by the Mann Whitney U test.

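### Couples are randomised and counted, but the primary endpoint and its planning SD are worded per embryo: fix the unit of the Wilcoxon test and restate the power basis

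*Protocol article*

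**What the plan says.** - **Unit of randomisation.** Under Randomisation, the protocol article allocates couples to the two arms.
- **Endpoint.** Under Primary and secondary endpoints, the wording is: "The primary endpoint is the mean period in hours for the cleaved embryos from participants in each arm of the study". The interval timed is that from two cells to three (CC2). Sample size and power considerations restates the endpoint as a difference in mean CC2 of embryos. Neither place names a value per couple.
- **Test.** Under Data analysis: "Differences in embryo quality parameters will be tested by Wilcoxon testing". No unit is given. The adjusted analyses list covariates but say nothing about several embryos from one couple.
- **Planning values.** The target in Sample size and power considerations is worded "detect a minimum absolute difference of 12% (1.4 hours) in mean CC2". The section also expresses it as an effect size of 0.670, and sets power at 80% or more and the significance level at 5%. The only SD there is attached to a report on embryos: "pooled SD 2.25 hours, but not normally distributed". The result is "a requirement of 46 couples per group in the analysis".

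**The concern.** A couple usually contributes several embryos, and these share parents, stimulation cycle and diet. Their CC2 values are therefore likely to be correlated, and a Wilcoxon test needs independent observations. The unit must be the same in the endpoint, the test and the sample size. Here the endpoint and the SD point to embryos, the randomisation and the count point to couples, and the test points to neither.

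Two things are at stake. The first is the type I error of the primary comparison, if an analyst follows the endpoint wording literally and pools embryos; couples with many embryos would then also carry more weight. The second is the meaning of the power statement, because an SD of single embryos is not the SD of a couple's average.

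**Working it through.** **Inputs from the protocol (Sample size and power considerations).** Difference 1.4 h; SD 2.25 h, quoted for embryos; effect size 0.670; power 80%; alpha 0.05, taken as two-sided because sidedness is not stated; 46 couples per group.

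**Inputs assumed.** Cleaved embryos per couple (m) and ICC are not in the document, so ranges are used. Normality is assumed for the arithmetic, although the protocol says CC2 is not normal.

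**1. Reproducing the plan's figure.**
- Standardised difference: 1.4 / 2.25 = 0.622.
- P(X<Y) = Φ(0.622 / √2) = Φ(0.440) = 0.670. This is the stated effect size.
- Noether's formula, per group: (1.960 + 0.842)² / [3 × (0.670 − 0.5)²] / 2 = 7.849 / 0.0867 / 2 = 45.25, so 46.

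Both stated figures match. The 0.670 is thus the probability that a value from one arm lies below a value from the other, not a standardised difference. Read as a standardised difference, it would imply an SD of 1.4 / 0.670 = 2.09 h, which the protocol does not give, and 80% power would need only about 35 to 42 per group depending on the formula. (At 85% power Noether's formula with 0.670 would give 45.1, again 46, but 85% is not stated, and an SD of 2.09 h is still close to the embryo figure.)

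**2. What this implies.** Each couple enters as one observation with SD 2.25 h. For a mean over m embryos, with 2.25 h as the total embryo SD,

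SD of couple mean = 2.25 × √[ICC + (1 − ICC)/m].

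This equals 2.25 only if m = 1 or ICC = 1.

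**3. If couple means are compared.** With 46 per group and 80% power, Noether's formula inverts to P(X<Y) = 0.5 + √[7.849 / (3 × 92)] = 0.669, a standardised difference of 0.617. The detectable difference is 0.617 × SD.

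| m | ICC | SD of couple mean (h) | 1.4 / SD | Detectable difference (h) |
|---|---|---|---|---|
| 3 | 0.1 | 1.42 | 0.98 | 0.88 |
| 3 | 0.3 | 1.64 | 0.85 | 1.01 |
| 6 | 0.1 | 1.12 | 1.24 | 0.69 |
| 6 | 0.3 | 1.45 | 0.96 | 0.90 |
| 8 | 0.1 | 1.04 | 1.35 | 0.64 |
| 8 | 0.3 | 1.40 | 1.00 | 0.86 |

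Power for 1.4 h, using the lower-bound Wilcoxon efficiency of 0.864, is about 96% to over 99% across these settings; on that basis the detectable differences run from 0.66 to 1.05 h. Over a wider range (3–10 embryos, ICC 0.05–0.5), power is about 92% to over 99%, and about 9 to 33 couples per group would suffice for 1.4 h.

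**4. If embryos are pooled as independent.** Simulated type I error at nominal 5%, with 46 couples per arm, embryo numbers varying between couples, and 1,500 runs per setting:

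| Mean m | ICC 0.05 | ICC 0.1 | ICC 0.2 | ICC 0.3 |
|---|---|---|---|---|
| 4 | 8.5% | 9.8% | 15.2% | 20.6% |
| 6 | 8.6% | 12.2% | 21.5% | 26.8% |
| 8 | 11.1% | 15.7% | 24.9% | 33.6% |

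The Wilcoxon test on couple means stayed at 3.7–5.5%. The closed form with equal embryo numbers, 2 × [1 − Φ(1.96 / √(1 + (m − 1) × ICC))], gives 6.8% at m = 4, ICC 0.05, and 26.6% at m = 8, ICC 0.3. It is lower because unequal embryo numbers add to the inflation. Every setting exceeds 5%.

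**The case against.** The best defence is that the couple is already the intended unit. The sample size section ties the Wilcoxon comparison to a number of couples in the analysis, and its attrition allowance covers couples without enough viable embryos, which suits one observation per couple better than a pool of embryos. The endpoint sentence can be read as a mean for each participant. A condensed article may also leave the per-couple summary or a clustering term to a fuller document, and the adjusted analyses do not exclude one. Much of this stands: it makes the couple reading plausible, and silence on clustering is not in itself the fault.

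Two things remain. The endpoint as printed averages over embryos by arm, so pooling is open to an analyst who follows it. And on the couple reading the planning SD is still that of single embryos; a later analysis plan could settle the test but would not correct the published calculation.

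A reader might infer that the primary test will have a false-positive rate of 8–34%. The document does not support that, because it never says embryos are the unit of the test. A reader might also infer that a couple-level analysis falls short of the stated power. The opposite holds: averaging lowers the SD, so the claim of at least 80% power for 1.4 h remains true and is understated.

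The sizes depend on assumed embryo numbers and ICC. They also take 2.25 h as the total embryo SD, although the protocol calls it pooled and does not say over which groups.

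**Conclusion.** The point holds as an inconsistency of unit between the endpoint, the test and the power basis. That an embryo SD served as the SD of one value per couple follows from the protocol's own figures and needs no assumed ICC. The consequence depends on the reading. Pooling would invalidate the nominal 5% level throughout the range examined. Comparing couple means would be valid, with 46 per group more than 1.4 h requires. It is therefore neither a demonstrated inflation of type I error nor a shortage of couples. It still needs correcting, because the validity of the primary test turns on a choice that the text leaves open.

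**What to change.** 1. Define the primary endpoint as one CC2 summary per couple, either the mean or the median over that couple's cleaved embryos (name which), compared between arms by the planned Wilcoxon test.
2. Apply the same rule to S2, T5, CC3 and the pronuclear timings.
3. Use an embryo-level model with a couple random effect only as a named secondary or adjusted analysis. It is not interchangeable with a Wilcoxon test on couple summaries: it weights couples differently and in its usual form assumes normality.
4. Restate the power paragraph with a couple-level SD, 2.25 × √[ICC + (1 − ICC)/m], over a range of ICC and m. Label 0.670 as P(X<Y), and give the resulting power for 1.4 h and the detectable difference with 46 couples per group. If a median is chosen, note that the formula is for a mean.

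The cost is wording in the endpoint, analysis and sample size sections. No further couples or data are needed, and the recruitment target can stay.

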### Randomisation

After collection of baseline data in the cycle prior to the intervention commencing, participating couples will be randomised to one or other of the study arms. The research team will be blinded to the randomisation. Stratification will be performed at randomisation for planned mode of fertilisation: in vitro fertilisation or intra-cytoplasmic sperm injection.

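### T5 is timed from fertilisation, but conventional IVF and ICSI share no observed moment of fertilisation, so this secondary endpoint has no common time zero

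*Protocol article*

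**What the plan says.** All places are in the protocol article.

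- **Primary and secondary endpoints.** The primary endpoint, CC2, is the interval from the 2-cell to the 3-cell stage. The secondary endpoints include S2, CC3, "T5 (time between fertilisation and the five cell embryo formation") "and the appearance and disappearance of the pronuclei". No time zero or unit is given for the pronuclear events.
- **Study population and recruitment.** Eligible women are "undergoing their first or second cycle of IVF or in vitro fertilisation – intracytoplasmic sperm injection (IVF-ICSI"), so both modes are in the trial.
- **Randomisation.** "Stratification will be performed at randomisation for planned mode of fertilisation: in vitro fertilisation or intra-cytoplasmic sperm injection".
- **Study design.** The laboratory description mentions "cumulus cells that are routinely removed, during IVF-ICSI, from the oocyte prior to insemination". It describes no such step for conventional IVF. During incubation, "twenty one plane focal images will be generated every hour". The time at which oocytes enter the time-lapse incubator is not given for either mode.
- **Data analysis.** Univariate and multivariate analyses are planned "In order to adjust for pre-defined confounders such as age, AMH level, ovarian stimulation method, fertilisation method and the number of oocytes obtained", and these cover the secondary outcomes. Embryo quality parameters are compared by Wilcoxon testing, with no mention of strata.

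**The concern.** T5 needs a start time. With ICSI, the injection is a timed laboratory act. With conventional IVF, sperm and oocyte are brought together and entry follows at a moment nobody records; only the insemination time is known. This follows from what the two procedures are, although the article does not spell it out. A time from fertilisation is therefore not the same observed quantity in both modes. Whatever substitute is used for IVF adds an offset relative to ICSI, plus oocyte-to-oocyte variation, and neither reflects embryo development.

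Pronuclear appearance raises a related question. If the cumulus is removed before insemination only with ICSI, the pronuclei may form out of view in some conventional-IVF oocytes, and the event would then be missing by mode.

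At stake are the precision of T5 and the completeness of one other secondary endpoint. CC2, CC3 and S2 describe intervals or synchrony between observed divisions and need no fertilisation time.

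**Working it through.** **1. The plan's own figure.** The article gives no SD, target effect or power for T5. Its only computed design figure is the CC2 sample size. With a difference of 1.4 h and SD 2.25 h, P(X<Y) = Φ((1.4/2.25)/√2) = Φ(0.622/√2) = 0.670. Noether's formula, two-sided 5% level and 80% power, gives n = (1.960 + 0.842)² / (6 × (0.670 − 0.5)²) = 45.3, so 46 per arm, as stated. This figure does not depend on T5.

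**2. Noise from a constant offset.** If a share q of couples has IVF and their clock is shifted by d hours, the between-couple SD rises from s to √(s² + q(1 − q)d²). At q = 0.5 the offset alone contributes an SD of d/2: 0.5 h for d = 1 h and 2 h for d = 4 h.

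None of the following inputs is in the article: q = 30% or 50%, d = 1, 2 or 4 h, T5 within-mode SD s = 3, 5 or 7 h, and a true effect of 0.67 s. With 46 per arm, normal-approximation power is Φ(0.67 s/SD × √(46/2) − 1.96). Adjusted for mode (SD = s), this is Φ(3.213 − 1.96) = 89.5%. Unadjusted, at q = 50%:

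| s (h) | d = 1 h | d = 2 h | d = 4 h |
|---|---|---|---|
| 3 | SD 3.04, 88.7% | SD 3.16, 86.2% | SD 3.61, 76.2% |
| 5 | SD 5.02, 89.2% | SD 5.10, 88.3% | SD 5.39, 84.7% |
| 7 | SD 7.02, 89.3% | SD 7.07, 88.9% | SD 7.28, 87.1% |

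At q = 30% the losses are slightly smaller; for example, s = 7 h and d = 4 h gives 87.5%. The effect of 0.67 SD is illustrative. The plan's 0.670 is a probability, and its CC2 target is 0.62 SD.

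**3. Bias between arms.** With modes balanced across arms, a constant offset cancels and the bias is 0. If the arms differed by 5 of 46 couples in the mode actually used, the unadjusted arm difference would shift by d × 5/46 = 0.11, 0.22 or 0.43 h for d = 1, 2 or 4 h. Adjustment for the mode actually used removes this; the article does not say whether its covariate is planned or actual mode.

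**4. What adjustment cannot remove.** A mode term absorbs the average offset but not the variation in sperm-entry time among IVF oocytes. The documents give no basis for sizing that variation.

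**5. Pronuclear appearance.** As an outer bound, suppose it were filmed only in ICSI couples. With an IVF share of 30% to 50%, 46 per arm falls to 46 × 0.7 ≈ 32 or 46 × 0.5 = 23. For 0.67 SD, power is Φ(0.67 × √16 − 1.96) = Φ(0.72) ≈ 76%, or Φ(0.67 × √11.5 − 1.96) = Φ(0.31) ≈ 62%. The article does not say that the loss is this large.

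**The case against.** The strongest reply is that the plan already handles most of this. Randomisation is stratified by planned mode, and fertilisation method is a named covariate for the secondary outcomes. A constant offset therefore neither biases the arm comparison nor survives the adjusted analysis. The primary endpoint and the sample size are untouched. A condensed article may also leave annotation rules and the start of recording to the full protocol or laboratory procedures.

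Most of this stands, and it limits the point to precision and completeness. It does not remove it. The article states the definition of T5, and that definition names an event that is not observed in one of the two modes. The Wilcoxon comparison is not described as stratified, and no adjustment restores an event that was never filmed.

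Three stronger readings are tempting, and the documents support none of them:

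- *Pronuclear appearance is also timed from fertilisation.* Only T5 is tied to fertilisation; the pronuclear events have no stated time zero.
- *Pronuclear appearance is largely unobservable in the IVF stratum.* That depends on cumulus status and loading time in conventional IVF, which the article does not give. Describing cumulus removal before insemination only for IVF-ICSI makes some loss likely, but its extent is unknown.
- *The arm comparison is biased.* Stratification and adjustment guard against that.

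**Conclusion.** The point holds as a modest one on secondary endpoints. T5, as defined, has no common observed time zero across the two modes. The consequence is extra noise: the offset in an unstratified Wilcoxon test, and within-IVF variation in sperm entry in any analysis. On the assumed values, the offset costs at most about 3 percentage points of power for 1 to 2 h and about 2 to 13 points for 4 h, with the largest loss when the T5 SD is small. The within-IVF part is not quantified.

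Pronuclear appearance is likely to be incomplete in conventional IVF, to an extent the documents do not give. The premise that sperm entry is timed only in ICSI rests on the nature of the procedures. The offsets, IVF shares and T5 SDs are assumptions.

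**What to change.** Settle these before any results by arm are seen:

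1. Time T5 from pronuclear disappearance, which is already a listed endpoint. The laboratory should confirm that this event is filmed in both modes, since the article does not give loading times.
2. Compare T5 between arms with a Wilcoxon test stratified by fertilisation mode, and say whether planned or actual mode is meant there and in the adjusted model.
3. Analyse pronuclear appearance only in the mode in which it is filmed, and state its time zero.
4. Keep T5 from injection (ICSI) or insemination (IVF) as a supportive analysis by mode, using the mode actually used, because that sets the clock.

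**Cost.** Endpoint and analysis wording, with times read from video that is recorded anyway; no new measurement and no change to the primary analysis or sample size. There are two downsides. The re-anchored T5 is less comparable with publications timed from insemination, and it excludes any diet effect before pronuclear disappearance. The supportive analysis covers both.
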